#### Secondary endpoints

All secondary outcomes are assessed for the past week at assessments 0 to 12.

##### Methamphetamine craving

Methamphetamine craving is assessed using the total score on the Craving Experience Questionnaire (CEQ), which has been validated for various substances [32]. The original CEQ has ten items: three items corresponding to the urge to use the substance, three items corresponding to intrusive thoughts and four items corresponding to the sensory aspects of substance use (e.g., picture, taste, smell and feel). The sensory items were adapted for methamphetamine and combined into three items: (1) taste and smell combined, (2) picturing methamphetamine and (3) imagining what it would feel like to smoke or inject it. This gave a total of nine items, each with scores ranging from 0 to 10 with higher scores representing a more severe craving.

##### Severity of methamphetamine dependence

The severity of methamphetamine dependence is assessed using the total score on the Severity of Dependence Scale (SDS) [33]. The SDS is a five-item scale that yields scores from 0 (no dependence) to 15 (most severe dependence). It has good internal consistency for amphetamine use (Cronbach’s alpha from 0.81 to 0.89) [33] and has been validated against a diagnosis of severe amphetamine dependence using the Composite International Diagnostic Interview (CIDI) [34].

##### Methamphetamine withdrawal symptoms

Methamphetamine withdrawal symptoms are assessed using the total score on the Amphetamine Withdrawal Questionnaire (AWQ) [35]. The AWQ is a ten-item questionnaire that rates various symptoms associated with amphetamine withdrawal on a five-point Likert scale. Scores range from 0 to 40 with higher scores indicating higher severity. The AWQ has a test–retest reliability of 0.79 and has been validated against other measures of withdrawal [35].

##### Psychiatric symptoms

Psychiatric symptoms are assessed using the Brief Psychiatric Rating Scale (BPRS) [36]. Symptom domains are rated against anchor points from 1 (nil) to 7 (extremely severe). Scores of 4 or greater indicate symptoms of clinical significance or pathological intensity. The BPRS has an inter-rater reliability of 0.83 when quality assurance procedures are followed [37]. The following endpoint definitions were used:Psychotic symptoms: A score of 4 or greater on any of the BPRS items of suspiciousness, unusual thought content and hallucinationsHostility: A score of 6 or 7 on the BPRS hostility itemDepression: A score of 4 or greater on the BPRS depression itemSuicidality: A score of 4 or more on the BPRS suicidality item

### Other assessments

#### Polysubstance use

The polysubstance use measure is the percentage of days using drugs from other classes (tobacco, alcohol, cannabis, cocaine, ecstasy, hallucinogens, inhalants and heroin) for the 28 days prior to assessments 0, 4, 8 and 12, assessed weekly using the TLFB, and averaged across drug types.

#### Adverse events

AEs will be assessed at each weekly assessment using open-ended questions and may include any other events that come to the attention of the trial staff during the trial. The outcome will be the number and percentage of participants reporting AEs and SAEs by System Organ Classification, coded according to the Medical Dictionary for Regulatory Activities. AEs will be counted once only for a given participant. The event counted will be the event with the highest severity (coded mild, moderate or severe).

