NAC’s well-established safety profile means that it can be delivered as a take-home medication [28], making it a potentially scalable and cost-effective treatment option. It is no longer under any patent restrictions, further enhancing its roll-out and take-up. Known adverse reactions include gastrointestinal upsets and rash [29], which have not been significantly elevated relative to the placebo in current NAC trials for substance use disorders [30]. The seemingly generic effect of NAC on drug craving suggests that it may also be helpful in managing polysubstance dependence.

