### Statistical considerations

#### Sample size estimation

The sample size of 90 participants per treatment arm is designed to detect a mean between-group difference of 3.5 days versus 6.0 days of methamphetamine use per month during the 12-week trial medication period with at least 80% power at *p* < 0.025 (0.05 / 2 to accommodate two primary outcome measures) and with 20% attrition (i.e., a final sample of at least 72 participants per treatment arm). The expected effect size is based on data from the Methamphetamine Treatment Evaluation Study (MATES) [42]. Participants who did not receive treatment in that cohort showed a reduction in methamphetamine use from a mean (standard deviation) of 12.8 (7.4) days per month at baseline to 6.0 (6.7) days per month at the 12-weekfollow-up. Our estimate of a minimal clinically meaningful reduction in use is based on outcomes for outpatient counselling derived from MATES: 11.2 (8.8) days per month to 3.5 (6.9) days per month at 12 weeks. Our estimate of 20% attrition is based on our previous research [42, 50, 51]. No interim analyses are planned. Statistical power was estimated using the SAMPSI command in Stata (Version 14.2, StataCorp LLC, College Station, Texas).

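### As written, the adverse-event rule counts each participant once, at their single worst event, so the System Organ Class percentages can understate incidence when a participant has events in more than one class

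*Protocol article*

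**What the plan says.** All of this is in the Adverse events subsection of Other assessments in the protocol article. The outcome comes first: "The outcome will be the number and percentage of participants reporting AEs and SAEs by System Organ Classification". The counting unit and the choice of event to keep follow: "AEs will be counted once only for a given participant. The event counted will be the event with the highest severity", on a three-grade scale from mild to severe. The unit is the participant and the retained event is singular. Neither this subsection nor any other part of the article limits the rule to within a class.

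Two other statements bear on the point. Collection is frequent and open: "AEs will be assessed at each weekly assessment using open-ended questions", and Table 1 shows AE collection at assessments 1 to 12. The Introduction also says: "Known adverse reactions include gastrointestinal upsets and rash". Aims and hypotheses makes an acceptable AE profile relative to placebo one of the secondary hypotheses.

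**The concern.** A class percentage should answer the question of how many participants had an event in that class. If only one event per participant is kept, the row instead shows how many participants had their worst event in that class. The two agree only for people whose events all fall in one class. With twelve open-ended enquiries, events in several classes are to be expected in some participants, and the two named reactions belong to different classes.

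Three things are at stake.

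- Class incidence would be understated.
- The understatement depends on what else a participant experienced. If that differs between arms, the comparison of arms is distorted as well as the level.
- Severity grade is not seriousness. If the rule runs across all events, an SAE graded moderate gives way to a non-serious event graded severe, although SAEs are also to be shown by class. The text has no rule for equal severity in two classes either, so the row chosen would then be arbitrary.

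**Working it through.** The article states no AE incidence, margin or AE-based power, so there is no figure of its own to reproduce. Every rate below is an assumption, used only to show how the literal rule behaves. The one input from the article is 90 participants per arm (Sample size estimation).

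**Step 1: one class, mild events.** Let a share p of an arm have a mild skin event. Let a share q of those people also have a worse event in another class. The literal rule shows p × (1 − q); the once-per-class rule shows p. With p = 10% and 90 per arm, the true count is 9.

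- q = 20%: 9 × 0.8 = 7.2 (8.0%)
- q = 40%: 9 × 0.6 = 5.4 (6.0%)
- q = 60%: 9 × 0.4 = 3.6 (4.0%)

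The relative loss equals q by construction, so this step shows the mechanism and says nothing about the likely size.

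**Step 2: three classes.** Assume independent classes, the same severity mix in each, and ties split at random. Given an event in one class, each class in which the person has an event is then equally likely to supply the kept event. If the other two classes have incidences b and c, the chance that the event of interest is kept is

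(1 − b)(1 − c) + [b(1 − c) + c(1 − b)]/2 + bc/3 = 1 − (b + c)/2 + bc/3.

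With gastrointestinal (GI) 30%, skin 10% and other 40%, the GI row keeps 1 − 0.25 + 0.0133 = 0.763, giving 22.9%. The skin row keeps 1 − 0.35 + 0.04 = 0.69, giving 6.9%.

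| Assumed GI / skin / other | GI reported (loss) | Skin reported (loss) |
|---|---|---|
| 10 / 3 / 15% | 9.1% (9%) | 2.6% (12%) |
| 30 / 10 / 40% | 22.9% (24%) | 6.9% (31%) |
| 30 / 10 / 70% | 18.7% (38%) | 5.7% (43%) |
| 30 / 15 / 90% | 15.6% (48%) | 7.4% (51%) |

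Check on the second line: the other row keeps 1 − 0.20 + 0.01 = 0.81, giving 32.4%. The three rows then sum to 22.9 + 6.9 + 32.4 = 62.2%. That equals the share with any event, 1 − 0.7 × 0.9 × 0.6 = 62.2%, as it must when each person appears once. The true class incidences sum to 80%.

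**Step 3: difference between arms.** Take true rash incidence of 10% on NAC and 5% on placebo, and apply Step 1.

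- q = 30% in both arms: 7.0% v 3.5%
- q = 50% v 30%: 5.0% v 3.5%
- q = 60% v 20%: 4.0% v 4.0%, and the excess is no longer visible

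**Step 4: the once-per-class rule.** In every scenario the row returns the true incidence, whatever q or the other classes are. In Step 1 that is 9 of 90 throughout.

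**The case against.** The strongest reply is that the counting sentence directly follows an outcome defined by System Organ Class and can be read as elaborating it: several events in one class count once in that class, at the worst grade. Both sentences then hold and the percentages are right. This reading is plausible and is the usual convention, so a reader who infers that the two sentences cannot both be true goes too far. What stands is that the text does not say it, and the words as printed direct something else.

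A second reply is that this is a condensed article and that Analysis of secondary outcomes leaves final analysis details to a statistical analysis plan. That is a fair answer to any request for preferred-term rows, an any-AE row, event totals or a fuller tie rule; those are additions and are not asked for here. It does not answer a counting rule that the article itself states and that, followed literally, does not produce the outcome it defines.

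A third reply concerns consequences, and much of it stands. All AEs are recorded at each assessment and reviewed by the trial physician, the data and safety monitoring board reviews participant safety, and the treatment satisfaction questionnaire assesses tolerability. No AE margin is stated. The Introduction's case for take-home use rests on a safety profile it treats as already established. The issue is the reported table; the documents do not support an inference that participants are less protected or that data are lost.

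**Conclusion.** The point holds as a defect of wording with a real consequence if followed literally: the class rows would show participants by worst event, and SAEs could be displaced by non-serious events of higher grade. Whether the sponsor intends this cannot be settled from the article.

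The size cannot be derived from the documents. In the assumed three-class scenarios, the loss runs from 9% to 51% of true class incidence, so roughly 10% to 50%. It depends on the assumed incidences, independence between classes, an equal severity mix and random ties. A reader might infer that at least a quarter of GI and skin incidence must disappear. That comes only from the higher assumed rates; the lowest scenario loses 9% to 12%. A reader might also infer that NAC's known reactions are lost preferentially because they are mild. The Introduction does not grade them, and it reports that they were not significantly elevated over placebo in current NAC trials for substance use disorders. The loss in Step 2 arises without that premise. Differential masking between arms is possible but not shown.

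**What to change.** Replace the two counting sentences with: *Each participant will be counted once within each System Organ Class, at the highest severity within that class.* State that the rule is applied separately to AEs and to SAEs, so that severity grade cannot displace seriousness. If the once-per-class rule was intended all along, this only makes it explicit.

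The cost is one sentence and standard table code. AEs are already collected weekly, graded and coded by class, so no new data are needed.

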#### Adherence

eCAP™ (Med-ic eCAP™, Information Mediary Corp) will be used as an objective measure of medication adherence. eCAP™ lids fitted to the medication bottles used record the times when a bottle is opened, which are downloaded at each assessment using a near-fieldcommunication-enabled smartphone and on bottle return using a CertiScan RFID desktop Reader (Med-ic Certiscan Version 2.5.1; Information Mediary Corp 2014–2018). Adherence will be the percentage of compliant doses, based on bottle opening, with dosing timeframes being morning (until 12 noon) and night (until midnight), or equivalent 12-h intervals.

#### Treatment satisfaction

The Treatment Satisfaction Questionnaire for Medication (TSQM) [38] will be completed at assessments 4, 8 and 12.

#### Concomitant treatments

All medications, including supplements, taken during the trial and all treatments related to either substance use or other mental health conditions received during the trial will be recorded on a template adapted from the National Institutes of Health’s concomitant medications form [39].

#### Health Economics

Data for costing are being collected to facilitate a subsequent economic evaluation of the intervention. These costing data include the EuroQol (EQ-5D-5L) [40] version 2.1, the Work Productivity and Activity Impairment Questionnaire – General Health V2 (WPAI-GH), and health service use and contact with the criminal justice system, which are assessed using a structured questionnaire. The data are updated weekly throughout the 12-week trial medication period.

#### Demographics, drug use and psychiatric history

Demographics, drug use and psychiatric history data are collected at the eligibility assessment. Demographics and drug use questions are based on the Opiate Treatment Index [41] and previous drug treatment trials [42], and include days of use for all major drug types in the past month. Current DSM-IV methamphetamine dependence is confirmed using CIDI [43]. The Mini International Neuropsychiatric Interview (MINI) [44] for Schizophrenia and Psychotic Disorders Studies, English Version 7.0.1, is used to screen for psychotic and affective disorders. Other measures include family history of psychotic disorders, assessed using the Diagnostic Interview for Psychosis (DIP) [45], the Readiness to Change Questionnaire (RCQ) [46], the Beck Cognitive Insight Scale (BCIS) [47], four items from the Birchwood Insight Scale (BIS) [48], and the Standardised Assessment of Personality – Abbreviated Scale (SAPAS) [49].

### Governance and ethical considerations

#### Quality control

All trial researchers will receive training in the trial assessment procedures. BPRS ratings are reviewed weekly, and a selection of ratings (10%) are audio-recorded and rated by an independent trained BPRS rater to establish inter-rater reliability. Primary endpoints are double entered. Weekly researcher meetings and monthly investigator meetings are held to monitor recruitment, follow-up, data collection and other trial procedures. A delegate from the coordinating sponsor institution (Curtin University) is responsible for conducting site visits (prior to initiation, during the trial and at trial completion) to audit compliance with the protocol and the accuracy and completeness of the data.

#### Data safety and monitoring board

The DSMB meet at least semi-annually and include individuals with expertise in the clinical topic area (methamphetamine and other substance use disorders), randomised clinical trials and biostatistics. The current DSMB also includes a consumer/community representative. The role of the DSMB is to review participant safety, recruitment, accrual, retention and withdrawal. The DSMB can recommend trial suspension, modification or discontinuation.

#### Data management

Personal information obtained from participants is stored securely and separately from trial data at the trial site and is accessible only to trial staff from that site. Participants’ trial data are de-identified using a unique study identifier. Saliva samples are de-identified and destroyed after analysis. De-identified trial data are entered onto a centralised secure (password protected) online electronic database, Research Electronic Data Capture (REDCap), which is hosted on a secure Curtin University server. De-identified trial data are available to all trial investigators. All analyses are based on de-identified data and will be published in a way that participants cannot be individually identified. Trial participants will be provided with a summary of their results at the close of the study. Otherwise, trial data are confidential and will be released in identified form only with the permission of the participant or as required by law. Trial data will be stored securely for 15 years after study completion; destruction of study material thereafter will be in accordance with local ethics approvals.

#### Ownership and publication

The ownership and permissions relating to the trial data are managed under a multi-institutional contractual agreement between the study sponsors, which is available on request from RM. The decision to publish information from the study will be made jointly by the trial investigators. Authorship will be in accordance with the guidelines of the International Committee of Medical Journal Editors. There are no other restrictions on the publication of trial results.

### Statistical considerations

#### Sample size estimation

The sample size of 90 participants per treatment arm is designed to detect a mean between-group difference of 3.5 days versus 6.0 days of methamphetamine use per month during the 12-week trial medication period with at least 80% power at *p* < 0.025 (0.05 / 2 to accommodate two primary outcome measures) and with 20% attrition (i.e., a final sample of at least 72 participants per treatment arm). The expected effect size is based on data from the Methamphetamine Treatment Evaluation Study (MATES) [42]. Participants who did not receive treatment in that cohort showed a reduction in methamphetamine use from a mean (standard deviation) of 12.8 (7.4) days per month at baseline to 6.0 (6.7) days per month at the 12-weekfollow-up. Our estimate of a minimal clinically meaningful reduction in use is based on outcomes for outpatient counselling derived from MATES: 11.2 (8.8) days per month to 3.5 (6.9) days per month at 12 weeks. Our estimate of 20% attrition is based on our previous research [42, 50, 51]. No interim analyses are planned. Statistical power was estimated using the SAMPSI command in Stata (Version 14.2, StataCorp LLC, College Station, Texas).

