#### Efficacy analysis

All tests will be two-sided with significance set at *p* < .025 for each of the two primary endpoints and *p* < .01 for each of the secondary endpoints. Significance for all other tests will be set at *p* < .05. The analyses will be conducted blind to condition.

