##### Analysis of primary outcomes

Intention-to-treat analyses will be conducted for the primary outcomes. The effect of the trial medication on days of methamphetamine use (percentage of days used in the past 28 days) will be tested using a baseline (assessment 0) vs. medication phase (three repeats: assessments 4, 8 and 12) by treatment condition (NAC vs. placebo). Unobserved days (e.g., due to hospitalisation or incarceration) will be censored. The effect of NAC on methamphetamine-positive saliva will be tested using a main effect for treatment condition (NAC vs. placebo) on saliva test results (positive vs. negative) from assessments 1–12 (12 repeats).

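### The stated power of at least 80% cannot be reproduced from the printed inputs and is not shown to apply to the baseline-by-phase contrast planned for days of use

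*Protocol article*

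**What the plan says.** In the protocol article, Sample size estimation says the design of 90 per arm is "designed to detect a mean between-group difference of 3.5 days versus 6.0 days of methamphetamine use per month". The power claimed for this target is worded as "during the 12-week trial medication period with at least 80% power at" the 0.025 level. That level is explained as "0.05 / 2 to accommodate two primary outcome measures". Attrition of 20% leaves "a final sample of at least 72 participants per treatment arm".

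The supporting figures come from a cited treatment cohort. Its untreated group went from "12.8 (7.4) days per month at baseline to 6.0 (6.7) days per month" and its outpatient-counselling group from "11.2 (8.8) days per month to 3.5 (6.9) days per month at 12 weeks", with SDs in brackets. Stata's SAMPSI command is named, but the article gives no method option, number of baseline and follow-up measures, or within-person correlation.

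Efficacy analysis fixes the sidedness: "All tests will be two-sided with significance set at" 0.025 for each primary endpoint. Analysis of primary outcomes says the effect on days of use "will be tested using a baseline (assessment 0) vs. medication phase (three repeats: assessments 4, 8 and 12) by treatment condition (NAC vs. placebo"). Analysis of secondary outcomes describes the same structure and calls it an interaction.

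**The concern.** The article prints every ingredient of a two-mean power calculation, yet those ingredients do not give the printed power. The missing ingredients are the ones that decide the answer: how baseline is used, how many follow-ups are averaged, and how strongly a person's measurements correlate. The primary contrast, as worded, is also the least favourable common way to use baseline unless the correlation is high.

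Aims and hypotheses describes the trial as powered to confirm a clinically relevant benefit, and Sample size estimation treats the counselling outcome as the smallest meaningful reduction. If power for the test actually run were well below 80%, a null result would be fairly likely even with that benefit present, and could be over-read as evidence against NAC.

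**Working it through.** **Inputs** (Sample size estimation unless noted)
- Difference: 6.0 − 3.5 = 2.5 days per month. Randomisation equalises expected baselines, so the same 2.5 days, taken as constant over the three follow-ups, is used for every analysis below.
- Mean follow-up variance: (6.7² + 6.9²)/2 = 46.25.
- Mean baseline variance: (7.4² + 8.8²)/2 = 66.10.
- Analysed per arm: 90 × 0.8 = 72, as the article states.
- Two-sided 0.025 (sidedness from Efficacy analysis): z = 2.241. For 80% power, z = 0.842.
- One baseline and three follow-ups (Analysis of primary outcomes).
- Correlations: none printed, so the values below are assumptions.

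**Formula.** Power = Φ(2.5/√(2V/n) − 2.241), where V is the per-person variance of the quantity compared. At n = 72, 80% power requires V ≤ 72 × 6.25/(2 × 3.083²) = 23.67, which is 0.512 of 46.25.

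**1. Trying to reproduce the stated 80%.** With V = 46.25:
- n = 72: 2.206 − 2.241 = −0.036, power 48.6%.
- n = 90: 2.466 − 2.241 = 0.225, power 58.9%.
- n for 80%: 2 × 46.25 × 3.083²/6.25 = 140.7, so 141 analysed per arm.

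Only a one-sided 0.05 test with all 90 per arm comes near (79.4%), and that contradicts both the stated level and the stated sidedness.

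**2. Planned contrast, read as an unconstrained difference in change, common correlation r.**
- Baseline SD equal to follow-up SD: V = 46.25 × [(1 + 2r)/3 + 1 − 2r] = 61.67(1 − r). V ≤ 23.67 needs r ≥ 0.616.
- Quoted baseline SDs: V = 66.10 + 46.25(1 + 2r)/3 − 2r × 55.15 = 81.52 − 79.47r, where 55.15 = (7.4 × 6.7 + 8.8 × 6.9)/2. V ≤ 23.67 needs r ≥ 0.728.

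**3. Baseline-adjusted model, common correlation r.** V = 46.25 × [(1 + 2r)/3 − r²]. The bracket is largest at r = 1/3, where it is 0.444. Then V = 20.56 and power is 85.7%, the minimum over all common correlations.

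| r | Change, equal SDs | Change, quoted baseline SDs | Baseline-adjusted |
|---|---|---|---|
| 0.5 | 67.7% | 53.2% | 88.0% |
| 0.6 | 78.2% | 63.2% | 91.4% |
| 0.7 | 89.4% | 76.0% | 95.7% |

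**4. Unequal correlations.** Let p be the correlation between follow-ups and b that between baseline and follow-up. The multipliers of 46.25 are (1 + 2p)/3 − b² (adjusted) and (1 + 2p)/3 + 1 − 2b (change, equal SDs).

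| p | b | Baseline-adjusted | Change, equal SDs |
|---|---|---|---|
| 0.7 | 0.4 | 69.7% | 48.6% |
| 0.6 | 0.4 | 74.9% | 51.7% |
| 0.7 | 0.5 | 76.8% | 58.9% |
| 0.6 | 0.5 | 82.4% | 63.1% |

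**5. Efficiency.** With baseline SD s and covariance c between baseline and the follow-up mean, the change variance exceeds the adjusted variance by (s − c/s)², which is never negative. Apart from the trivial cost of estimating the slope, adjustment cannot lose.

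**The case against.** The strongest reply is that this is an undisclosed input and not an error. SAMPSI accepts baseline and repeated measures. Its ANCOVA option with three follow-ups gives at least 85.7% at any common correlation. With one follow-up and r = 0.70, V = 46.25 × (1 − 0.49) = 23.59 and power is 80.2% at exactly 72 per arm. The article condenses a full protocol that is not shown and may state the options. This stands: a reader might infer from the 49% that the calculation is wrong or the trial underpowered, and the document supports neither. The 49% describes a single-time-point test that nobody plans; it shows only that the printed inputs are not enough.

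It can also be said that the primary-outcome sentence does not use the word interaction and does not say whether baseline means are constrained equal. A constrained-baseline mixed model also tests a phase-by-treatment contrast, with roughly ANCOVA efficiency, and the article leaves final analysis details to the statistical analysis plan. That is fair, so the thresholds of 0.62 and 0.73 are conditional on the unconstrained reading. It is still the natural one, since the secondary analyses call the same structure an interaction.

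Finally, 72 per arm may be pessimistic, because the primary analysis is intention-to-treat with multiple imputation. Yet with full information on all 90 per arm, the change contrast at r = 0.5 gives only 78% (V = 30.83; 3.020 − 2.241 = 0.779) or 64% (V = 41.78; 2.594 − 2.241 = 0.353).

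None of this ties the 80% to the contrast the article names.

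**Conclusion.** The concern holds in a limited form, as something that should be fixed. The printed inputs alone give about 49%, so the 80% depends on assumptions the article does not state. For the planned contrast, with baseline means unconstrained, 80% requires a common correlation of at least about 0.62 (equal SDs) or 0.73 (quoted baseline SDs). At r from 0.5 to 0.7, power runs from about 53% to 89%.

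These figures assume a constant 2.5-day effect, 72 analysed per arm, normal-theory tests and one common correlation, none of which can be checked against a printed correlation. They do not establish the trial's true power.

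A second tempting inference is that a baseline-adjusted model secures 80%. It does so under any common correlation. It falls short when follow-ups correlate clearly more with each other than with baseline: three of the four unequal pairs examined give about 70% to 77%, and the fourth 82%.

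**What to change.** - Specify the primary days-of-use analysis as a mixed model over assessments 4, 8 and 12 that adjusts for assessment 0 or constrains baseline means to be equal across arms.
- Restate the power for that model, giving the SAMPSI method, the number of baseline and follow-up measures, and separate assumed correlations for baseline to follow-up and between follow-ups. Show a range, and do not describe 80% as guaranteed.
- If the unconstrained interaction is kept, replace the claim of at least 80% with its power over a range of assumed correlations. If the full protocol already records the SAMPSI options, quote them and say whether they match the planned contrast.

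The cost is wording in the statistical analysis plan and the sample-size section, settled before unblinding, the point by which the article says that plan will be written. The model uses data already scheduled for collection and needs no extra participants. The stated power may become less favourable.

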### Aims and hypotheses

The aim of the current trial is to test the safety and efficacy of NAC as a pharmacotherapy for methamphetamine dependence using a double-blindplacebo-controlled randomised controlled trial. The trial will recruit 180 participants, who will receive either 12 weeks of oral NAC (2400 mg daily) or matched placebo. This is a phase IIb trial that is powered to confirm whether NAC has a clinically relevant benefit on methamphetamine use. The comparator condition is a matched placebo, with all participants provided with a minimal form of intervention (a self-help booklet), due to the lack of readily available standardised effective treatment options for methamphetamine use.

The primary hypothesis is that daily oral NAC delivered as a take-home medication will reduce methamphetamine use measured as (a) days of methamphetamine use and (b) methamphetamine-positive weekly saliva tests, during 12 weeks of active treatment relative to the placebo. The secondary hypotheses are that daily oral NAC delivered as a take-home medication will, relative to placebo:reduce the severity of methamphetamine dependence, the craving for methamphetamine, methamphetamine withdrawal symptoms and psychiatric symptoms (depressive symptoms, suicidality, psychotic symptoms and hostility)have an acceptable adverse event (AE) profilenot significantly increase the use of other substances (including alcohol, tobacco, cannabis, heroin and cocaine).

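### The 2.5-day target is the raw 12-week gap between two MATES groups that already differed by 1.6 days at baseline; allowing for baseline, the same figures give about 0.9 to 2.0 days

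*Protocol article*

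**What the plan says.** Under Sample size estimation, the trial is "designed to detect a mean between-group difference of 3.5 days versus 6.0 days of methamphetamine use per month" over the medication period, "with at least 80% power". It randomises 90 per arm and expects 72 per arm after 20% attrition, at an alpha of "0.025 (0.05 / 2 to accommodate two primary outcome measures"). Efficacy analysis makes the tests two-sided.

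The two means come from MATES, which the article calls a cohort. Members who went untreated moved from "12.8 (7.4) days per month at baseline to 6.0 (6.7) days per month" at 12 weeks. Those in outpatient counselling moved from "11.2 (8.8) days per month to 3.5 (6.9) days per month at 12 weeks". The article presents MATES as the source of the expected effect size, and the counselling outcomes as the source of its smallest clinically meaningful reduction. Both roles fall to the same 2.5 days.

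Aims and hypotheses describes the trial as "powered to confirm whether NAC has a clinically relevant benefit on methamphetamine use". Under Analysis of primary outcomes, days of use are tested as baseline versus medication phase (assessments 4, 8 and 12) by treatment condition, which is a contrast of changes from baseline.

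**The concern.** The target is framed as a reduction, but it is computed as a difference between end values. The paragraph prints two unequal baselines, 12.8 and 11.2 days, and then leaves them out of the calculation. Part of the 2.5-day gap at 12 weeks is therefore likely to reflect where the groups started rather than what counselling did. Randomised arms have equal expected baselines, so that part has no counterpart in a treatment effect in this trial.

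At stake is what the sample size can be said to deliver. If 2.5 days is larger than the counselling benefit that MATES shows, the stated power does not apply to a counselling-sized benefit. A reader who takes 2.5 days as the smallest effect that matters could then over-interpret a non-significant result.

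**Working it through.** **Inputs (Sample size estimation, Analysis of primary outcomes).** Untreated 12.8 (7.4) to 6.0 (6.7); counselling 11.2 (8.8) to 3.5 (6.9); 72 analysed per arm; two-sided alpha 0.025, so z = 2.241; one baseline and three follow-ups. The within-person correlation r is not given. It is assumed common to all time points and varied.

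**Pooled SDs.** Baseline: sqrt((7.4² + 8.8²)/2) = 8.13. At 12 weeks: sqrt((6.7² + 6.9²)/2) = 6.80.

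**The plan's own figure.** Power = Φ(δ/SE − 2.241), with SE = 6.80 × sqrt(2f/72). The variance factor f is:
- single time point: f = 1
- change from baseline: f = (1+2r)/3 + 1 − 2r
- baseline-adjusted: f = (1+2r)/3 − r²

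For δ = 2.5, a single time point gives 49%. The baseline-adjusted form gives at least 85.7% at every r. The change form reaches 80% from about r = 0.62. The stated 80% is thus attainable with repeated measures, but the article gives neither the correlation nor the option used, so it cannot be reproduced exactly.

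**What MATES shows once baseline is allowed for.**
- Raw gap at 12 weeks: 6.0 − 3.5 = 2.5
- Gap at baseline: 12.8 − 11.2 = 1.6
- Reductions: 12.8 − 6.0 = 6.8 and 11.2 − 3.5 = 7.7; difference in change 7.7 − 6.8 = 0.9
- Regression-adjusted difference: 2.5 − 1.6 × r × 6.80/8.13. This is 1.96 at r = 0.4, 1.83 at 0.5, 1.70 at 0.6, 1.56 at 0.7 and 1.43 at 0.8

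**Power, 72 per arm, three follow-ups, SD 6.8 (change / baseline-adjusted).**

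| δ (days) | r = 0.4 | r = 0.5 | r = 0.6 | r = 0.7 | r = 0.8 |
|---|---|---|---|---|---|
| 0.9 | 9% / 15% | 10% / 16% | 12% / 17% | 16% / 21% | 24% / 28% |
| 1.8 | 32% / 56% | 38% / 59% | 47% / 64% | 61% / 73% | 80% / 86% |
| 2.5 | 59% / 86% | 68% / 88% | 78% / 91% | 89% / 96% | 98% / 99% |

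Worked cell: δ = 0.9, change, r = 0.8. f = 0.267, SE = 0.585, and Φ(0.9/0.585 − 2.241) = Φ(−0.70) = 24%.

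Pairing each adjusted MATES difference with its own r in the baseline-adjusted model gives 65% (r = 0.4), 60% (0.5), 58% (0.6), 59% (0.7) and 66% (0.8). Check at r = 0.5: f = 0.417, SE = 0.732, Φ(1.83/0.732 − 2.241) = Φ(0.26) = 60%.

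**Sensitivity.** If the baseline SD is 8.13 rather than 6.80, the change form gives 7% (r = 0.4) to 17% (r = 0.8) for 0.9 days. At r = 0.9 with SD 6.8, the baseline-adjusted model gives 51% for 0.9 days. The adjusted MATES difference is then 1.30 days, with 84% power, so the shortfall for the adjusted difference depends on r not being that high.

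**The case against.** The strongest reply is that 0.9 days is the lowest reading of MATES, not its answer. A reader might infer that 1.6 of the 2.5 days is pure baseline imbalance. That would require a follow-up-on-baseline slope of 1. The pooled SD falls from 8.13 to 6.80, so the slope is at most 6.80/8.13 = 0.84 even at r = 1, which leaves about 1.2 days. At r = 0.4 to 0.7 the imbalance explains only about 0.5 to 0.9 of the 2.5 days. This stands, and it is why a range is given. MATES group sizes are not printed either, so no interval can be put round any of these differences. In a cohort, neither change scores nor baseline adjustment isolates the counselling effect. That the groups were not randomised is inferred from the word cohort and the description of an untreated subgroup.

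The interaction test might also be thought to shrink the target. It does not: between randomised arms, a true 2.5-day effect is 2.5 days on the change scale too. A sponsor may choose to power for 2.5 days on clinical judgement.

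Other strong readings fail as well. A counselling-sized benefit would not almost surely be missed, since power for the adjusted difference is 58% to 65%. Nowhere does the article say that a null result excludes such a benefit; it speaks only of being powered to confirm whether there is one. Nor does it assume a full 2.5 days from the first month, because the target is a mean over the medication period.

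What the reply leaves untouched is the stated basis: 2.5 days is attributed to MATES, and the MATES figures printed beside it do not bear it out once baseline is considered.

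**Conclusion.** The derivation of the target is wrong as written. MATES, on the article's own figures, does not support 2.5 days as the counselling-equivalent effect, and so not as the expected or minimal effect drawn from it. Allowing for baseline gives 0.9 days on raw change, or about 1.6 to 2.0 days by regression adjustment at an assumed r of 0.7 to 0.4.

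For 0.9 days, power is about 9% to 24% (change) or 15% to 28% (baseline-adjusted) at r = 0.4 to 0.8. For the adjusted 1.6 to 2.0 days it is about 58% to 65% in a baseline-adjusted model. Both fall short of the stated 80%. These figures assume SD 6.8, a common correlation and 72 analysed per arm.

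This is a fault in how the assumption was derived and described. It is not an error in the power arithmetic for 2.5 days, and it does not show that the trial is too small for that effect.

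**What to change.** In the SAP, which the article says will be completed before unblinding, and in the trial report:

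1. Describe 2.5 days as a chosen target, and drop the statement that it is the expected or minimal effect derived from MATES.
2. State the baseline-corrected MATES differences: 0.9 days on change, and about 1.6 to 2.0 days adjusted, with the correlation assumed.
3. Give power at about 0.9, 1.8 and 2.5 days, naming the correlation and the repeated-measures method used.
4. State that a non-significant result will not be read as excluding a counselling-sized benefit unless the confidence interval does so.

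The cost is some rewording and less favourable stated figures. No extra patients and no change to the design or primary test are needed.
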